#### ***Secondary analyses***

As a secondary outcome, we will also assess change in transplant knowledge from 1 week post-evaluation to approximately three months after the transplant evaluation. In this analysis, the outcome will be measured as “difference scores” (the 1 week knowledge score subtracted from the three month knowledge scores) using linear regression with GEE and adjusting for unequally distributed baseline characteristics [54].

We will determine the impact of the study intervention upon the other secondary outcomes: (1) readiness to pursue transplant and LDKT at 1 week post-evaluation; (2) self-efficacy regarding transplant and LDKT at 1 week post-evaluation; (3) decisional balance regarding transplant and LDKT at 1 week post-evaluation; and (4) changes in readiness, self-efficacy, and decisional balance regarding transplant and LDKT, from 1 week to 3 months post-evaluation. Self-efficacy, decisional balance, and change in self-efficacy and decisional balance are measured on a continuous scale, so they will also be analyzed with linear regression with GEE. Readiness to pursue transplant and LDKT will be analyzed as dichotomous outcomes, where the probability of patients being in Action or Maintenance vs. the probability of being in Pre-contemplation, Contemplation, or Preparation will be modeled with logistic regression with GEE. The tests for all secondary outcomes will also be adjusted for any unbalanced baseline characteristics.

Finally, to examine how key barriers to LDKT work alone and in combination with our intervention to impact LDKT knowledge, we will test the independent effects of race, previous actions taken to learn about transplant, and health literacy on knowledge at 1 week post-baseline. We will also test whether these variables interact with the intervention to effect knowledge of LDKT. We will model knowledge of LDKT as the dependent variable using multivariable linear regression models with GEE. To fit the models, we will use forward selection procedures where independent variables that are univariately significant at P < 0.20 will be eligible for inclusion in the multivariable model. Those variables significant at P < 0.05 in the multivariable models will be retained [55].

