**Methods/design:**

We report the protocol of the Enhancing Living Donor Kidney Transplant Education (ELITE) Study, a cluster randomized trial of an educational intervention to be implemented during initial transplant evaluation at a large, suburban U.S. transplant center. Five hundred potential transplant candidates are cluster randomized (by date of visit) to receive either: (1) standard-of-care (“usual”) transplant education, or (2) intensive education that is based upon the *Explore Transplant* series of educational materials. Intensive transplant education includes viewing an educational video about LDKT, receiving print education, and meeting with a transplant educator. The primary outcome consists of knowledge of the benefits, risks, and process of LDKT, assessed one week after the transplant evaluation. As a secondary outcome, knowledge and understanding of LDKT are assessed 3 months after the evaluation. Additional secondary outcomes, assessed one week and 3 months after the evaluation, include readiness, self-efficacy, and decisional balance regarding transplant and LDKT, with differences assessed by race. Although the unit of randomization is the date of the transplant evaluation visit, the unit of analysis will be the individual potential transplant candidate.

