### Study aims

Our primary aim is to determine the effects of an educational intervention (intensive transplant education), versus standard-of-care (usual) transplant education, upon transplant candidates’ knowledge of the benefits, risks, and process of LDKT, assessed one week after transplant evaluation.

As secondary aims, this study will also determine differences in readiness, self-efficacy, and decisional balance regarding transplant at one week after transplant evaluation, between patients who receive intensive, versus usual, transplant education. The study will also examine how knowledge, readiness, self-efficacy, and decisional balance change between one week and three months, in patients who receive intensive, versus usual, transplant education. Finally, the study will also determine how known barriers to LDKT, including Black race, less prior transplant education, and lower health literacy, act alone and in combination with the educational interventions to affect patients’ level of knowledge at one week and three months.

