**Outcomes**				
Knowledge of transplant		X	X	
Readiness to pursue transplant		X	X	
Self-efficacy regarding transplant		X	X	
Decisional balance regarding transplant		X	X	

We are unable to measure study participants’ “baseline” knowledge, readiness, self-efficacy, and decisional balance regarding transplant, prior to starting the evaluation. This inability stems from human subjects IRB restrictions that prevent us from administering questionnaires by telephone to persons who have not provided written informed consent. In addition, on the day of the actual transplant evaluation, obtaining individual written informed consent from up to six transplant candidates, prior to the delivery of any actual education, is also infeasible. Therefore, due to human subjects limitations and practical concerns, we are unable to obtain baseline measures (of knowledge, readiness, self-efficacy, and decisional balance regarding transpland and LDKT) prior to the start of usual or intensive transplant education.

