#### ***Secondary outcome: change in knowledge of LDKT at 3 months after the transplant evaluation***

As a secondary outcome, we also assess change in knowledge of LDKT three months after the transplant evaluation. Knowledge at three months is assessed using the same 20-item questionnaire that we use at 1 week after the transplant evaluation. LDKT knowledge “difference” scores will be calculated by subtracting the 1 week post-baseline LDKT knowledge scores from the 3 month post-baseline scores.

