## Discussion

We designed the ELITE study to determine whether an educational intervention, implemented on the day of the transplant evaluation at the transplant center, increases knowledge of LDKT among potential transplant candidates, assessed one week and 3 months after the evaluation. Additional secondary outcomes include readiness, self-efficacy, and decisional balance regarding transplantation and LDKT, assessed one week and 3 months after the evaluation. We also will compare the effectiveness of the different educational interventions for Black and non-Black patients and patients of varying levels of health literacy.

This study is notable for testing an intervention that is physically delivered at the transplant center, in a method consistent with standard clinical care. If effective, more intensive transplant education could be replicated and easily incorporated into transplant evaluations in the approximately 235 transplant centers nationwide. Surprisingly, few interventions have targeted CKD patients being evaluated at the transplant center [42,56]. Instead, most prior interventions have targeted CKD patients in nephrologists’ offices [57,58], dialysis units [59,60], and patients’ homes [56,61]. By bringing together CKD patients who have some preexisting interest in transplant, the transplant evaluation, offers an opportunity to efficiently and effectively educate these patients about LDKT.

Our study design has several potential limitations. Our educational intervention is a relatively brief, one-time event that occurs solely at the transplant evaluation. Typically, the study participants in the intensive education arm will spend less than one hour watching videos and meeting with the Transplant Educator. An intervention that includes additional education sessions (e.g. after the transplant evaluation) may be more effective, albeit less practical. In addition, all study participants in the intervention arm receive the same intervention. If we were able to measure study participants’ knowledge and interest in LDKT prior to the transplant evaluation, then we could tailor the intervention for each participant’s level of readiness.

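### The only arm comparison specified for 3-month knowledge is the change from the 1-week post-intervention score, which measures retention and does not test whether knowledge is higher at 3 months

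*Protocol article*

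**What the plan says.** The 3-month knowledge outcome is defined and analysed in the same way in two places. The outcome section on 3-month knowledge states: "LDKT knowledge “difference” scores will be calculated by subtracting the 1 week post-baseline LDKT knowledge scores from the 3 month post-baseline scores". Secondary analyses makes that quantity, "the 1 week knowledge score subtracted from the three month knowledge scores", the dependent variable of a linear regression with GEE.

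The subtracted score is not a baseline. Both parts of the intervention take place on the evaluation day, and the first knowledge questionnaire is the telephone interview at 1 week. The Outcomes section says of knowledge and the other attitudinal measures that "we are unable to obtain baseline measures" before education starts. The 1-week score is itself the primary outcome.

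The article describes the 3-month question in three ways:

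- Study aims includes a secondary aim on "how knowledge, readiness, self-efficacy, and decisional balance change between one week and three months", by arm. The difference score matches this.
- The Abstract says: "As a secondary outcome, knowledge and understanding of LDKT are assessed 3 months after the evaluation". The Discussion says the study was designed to determine whether the intervention "increases knowledge of LDKT among potential transplant candidates, assessed one week and 3 months after the evaluation".
- Study aims also asks how barriers, alone and together with the intervention, act "to affect patients’ level of knowledge at one week and three months". The matching analysis tests the effects of "race, previous actions taken to learn about transplant, and health literacy on knowledge at 1 week post-baseline", so the only timepoint it names is 1 week.

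For self-efficacy and decisional balance, the article plans 1-week comparisons and a difference score from 1 week to 3 months. For readiness it lists change among the outcomes, but the only model it gives is a logistic GEE for a dichotomised stage.

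**The concern.** A change score normally removes a pre-treatment level. Here it removes a post-treatment level, and with it the effect of interest. Whether patients who had the intensive education know more at 3 months is a natural durability question, and the Abstract and Discussion present it as one the study addresses. No stated analysis compares the arms on the 3-month score, so the plan supplies no estimate, interval or test for it. If the investigators want that comparison after seeing the change result, it will be post hoc.

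**Working it through.** **Inputs from the protocol article.** Score range 0 to 20 (Primary analysis). Expected 1-week effect 10-20%, 250 patients per arm, about 100 evaluation days per arm with 2-3 patients each, ICC 0.4, type 1 error 0.05, power at least 95% (Power and sample size calculations).

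**Assumptions, because the article gives no figure.** 10-20% means percentage points of the 20-point scale, so D = 2 to 4 points. SD of the score is 3 to 5. Correlation rho between the 1-week and 3-month scores is 0.5 to 0.7. Tests are two-sided, all patients have both scores, and the same design effect applies to the level and to the change.

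**The plan's own power figure.** With 250/100 = 2.5 patients per day, the design effect is 1 + (2.5 - 1) × 0.4 = 1.6, and the effective n is 250/1.6 = 156.25 per arm. Power of 95% needs a standardised difference of (1.96 + 1.645) × √(2/156.25) ≈ 0.41 (0.38 to 0.43 for 2 to 3 patients per day). A 2-point difference meets this if the SD is about 4.9 or less (4.6 to 5.2). The claim is plausible but cannot be confirmed without an SD. The present point does not depend on it.

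**The estimand.** Let D be the 1-week arm difference and r the share of it retained at 3 months.

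- Arm difference in 3-month level = r × D
- Arm difference in change = r × D - D = (r - 1) × D

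The second expression is 0 at r = 1, negative for any r below 1, and positive only if r exceeds 1. These signs hold for any SD and any correlation.

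**Size, with D = 2 and SD 4.** SE of the level contrast = 4 × √(2/156.25) = 0.453. The SD of the change is SD × √(2(1 - rho)), that is 4.0 at rho 0.5 and 3.1 at rho 0.7, so the SE of the change contrast is 0.453 and 0.351.

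| Retained r | Level difference at 3 months | Power, level | Change contrast | Change significantly negative |
|---|---|---|---|---|
| 1 | +2.0 | 99% | 0 | 2.5% |
| 0.75 | +1.5 | 91% | -0.5 | 20-30% |
| 0.5 | +1.0 | 60% | -1.0 | 60-81% |

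At full retention the change contrast favours intensive education significantly only 2.5% of the time, which is the false-positive rate.

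**Sensitivity.** At half retention with D = 2, SD 3 gives 84% power for the level and 84-97% significantly negative change. SD 5 gives 42% and 42-63%. With D = 4, half retention and SD 4, the level difference is +2.0 with 99% power, and the change contrast of -2.0 is significantly negative at least 99% of the time.

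**Cross-check.** A clustered GEE simulation (300 runs, SD 4, ICC 0.4, rho 0.6, D = 2) gave a level of +2.00 and a change of +0.02 at r = 1. At r = 0.5 it gave +0.99 and -1.03, with the change significantly negative in 74% of runs.

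**Precision.** Var(change)/Var(score) = 2(1 - rho): 1.4 at rho 0.3, 1.0 at 0.5, 0.6 at 0.7. The change score may be more or less noisy than the 3-month score, so precision does not argue for either.

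**The case against.** The strongest defence is that the analysis does what one stated aim asks. Study aims wants the change between 1 week and 3 months by arm, the outcome section is headed as change, and the analysis models change. As a measure of retention the contrast is valid. That stands, and it is why the difference score should keep its test and interval.

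A second defence is that the 3-month comparison can be recovered: in patients with both scores and the same covariates, the 1-week effect plus the change effect equals the 3-month effect. This is true of the point estimate. The plan states no such sum, and its interval and test do not follow from the two separate results.

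Third, the sentences on interaction with the intervention name no timepoint, and Study aims mentions the level at three months, so a 3-month model might be meant. The sentence that opens that analysis names 1 week only, so this is at best an ambiguity. One might also say that the Abstract's wording describes measurement only. The Discussion sentence does not read that way: it asks whether the intervention increases knowledge at both times.

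A reader might infer that the plan will report a durable success as a failure, or partial forgetting as harm. The documents do not support that. Nothing says the coefficient will be read so, and the 1-week effect will be reported as the primary result. A negative change beside a positive 1-week effect means that part of the advantage has faded; by itself it does not mean that the intensive arm knows less than usual care at 3 months.

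**Conclusion.** The point holds as a mismatch between a stated question and the stated analysis. The article fixes the 3-month knowledge outcome as change from a post-intervention score, and that contrast, (r - 1) × D, cannot test whether knowledge is higher at 3 months. This rests on algebra and on the article's own text. The percentages rest on the assumed SD, correlation, 2- to 4-point effect and complete follow-up, and show only that a positive 3-month difference together with a significantly negative change contrast is a realistic result.

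The same gap exists for self-efficacy and decisional balance, where only the 1-week level and the difference score are planned. It might seem to extend to readiness in the same form, but no difference score is defined there. For readiness the article lists change without saying how it is constructed, and whether the 3-month level is compared is unclear.

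This should be fixed. It is not critical, because the primary outcome, sample size and data collection are unaffected.

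**What to change.** Add to Secondary analyses a GEE comparison of the arms on the 3-month knowledge score, clustered by evaluation date, as the secondary estimate of the effect at 3 months. Equivalently, fit one model to both interviews with arm, visit and arm-by-visit, and report the 3-month arm contrast with its interval.

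Keep the difference score from 1 week to 3 months as a separate inferential analysis. Label it as retention and state that it is to be read beside the 1-week effect.

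Add the same 3-month level contrast for self-efficacy and decisional balance, and compare dichotomised readiness at 3 months by logistic GEE. Make the Abstract, outcome definition and Discussion name both quantities.

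The cost is analysis wording. Table 1 already schedules all these measures at 3 months, so no new data are needed. The change should be made before arm-level results are seen.

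### The three named barriers and their interactions with the intervention are put through forward selection instead of being fixed in the model, so the promised comparison by race can go unreported

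*Protocol article*

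**What the plan says.** Study aims sets a secondary aim on three obstacles to LDKT: being Black, having had less earlier education about transplant, and having limited health literacy. The question is how these, in the article's words, "act alone and in combination with the educational interventions to affect patients’ level of knowledge at one week and three months". The Discussion repeats that the interventions will be compared for Black and non-Black patients and across levels of health literacy.

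Secondary analyses turns this into named tests: "we will test the independent effects of race, previous actions taken to learn about transplant, and health literacy on knowledge at 1 week post-baseline", followed by "We will also test whether these variables interact with the intervention to effect knowledge of LDKT". The tool is stated: "We will model knowledge of LDKT as the dependent variable using multivariable linear regression models with GEE". The way the models are built is then fixed: "we will use forward selection procedures where independent variables that are univariately significant at P < 0.20 will be eligible for inclusion", and "Those variables significant at P < 0.05 in the multivariable models will be retained".

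No sentence exempts arm, the three barriers or their interactions from this rule, and none says how an interaction term meets the univariate criterion.

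**The concern.** Selection is a way to search for predictors. Here the predictors and interactions are already named, so there is nothing to search for. Three things can go wrong.

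- A named barrier that misses P < 0.20 alone, or P < 0.05 jointly, leaves the model, and its effect is not estimated.
- A univariate screen sees a barrier's effect averaged over the arms. An interaction is the difference between the arms. A barrier that acts differently by arm can average out and never reach the interaction test.
- Terms kept because they were significant have estimates that tend to be too large, and p-values that take no account of the selection.

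At stake is whether the trial reports how well the education works in Black and non-Black patients, which its own aims and Discussion promise.

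**Working it through.** **1. The plan's own figure.** The only power statement (Power and sample size calculations) concerns the primary comparison: at least 95% with 250 per arm, about 100 days per arm, 2–3 patients per day and ICC 0.4. The design effect at 2.5 per day is 1 + (2.5 − 1) × 0.4 = 1.6, so the effective n is 250/1.6 = 156 per arm. The difference detectable at 95% power is (1.96 + 1.645) × √(2/156.25) = 0.41 SD. If 10% means 2 of 20 points, the claim holds for an SD up to 2/0.408 = 4.9. The SD is not given, so the 95% is plausible but cannot be reproduced. No power is given for the barrier or interaction tests.

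**2. What the screen sees.** Let a barrier have effect b0 in usual and b1 in intensive education. With equal arms its overall effect is (b0 + b1)/2, and the interaction is b1 − b0. With −0.2 and +0.2, the overall effect is 0 and the interaction is 0.4.

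**3. Simulation of interaction tests.** From the protocol: 200 days, 500 patients, 2–3 per day, ICC 0.4. Assumed: one binary barrier with 35% prevalence, an arm effect of 0.4 SD, and the barrier effects shown. Each scenario has 3,000 trials (Monte Carlo error about 1 percentage point), fitted by linear GEE with exchangeable correlation and robust standard errors. Here the barrier is screened and its interaction is tested only if it passes.

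| b0 / b1 (SD) | Barrier passes P < 0.20 | Interaction found: fixed model | After screen | Barrier must also have P < 0.05 |
|---|---|---|---|---|
| −0.2 / +0.2 | 19% | 67% | 12% | 3% |
| −0.3 / +0.3 | 20% | 94% | 19% | 4.5% |
| −0.3 / +0.1 | 45% | 67% | 30% | 13% |
| 0 / +0.3 | 69% | 43% | 28% | 18% |
| −0.4 / 0 | 86% | 67% | 57% | 44% |
| −0.5 / −0.1 | 98% | 66% | 65% | 62% |

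Hand check: power after the screen is close to pass rate × fixed-model power. Row 1: 0.189 × 0.668 = 0.126 (simulated 0.121). Row 3: 0.451 × 0.673 = 0.304 (0.302). Row 6: 0.984 × 0.659 = 0.648 (0.649).

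**4. Main effects, equal in both arms.** A true 0.1 SD fails the screen in 53% of trials and is kept in 22%; 0.2 SD fails in 15% and is kept in 65%; 0.3 SD is kept in 95%. The mean estimates when kept are 0.21, 0.25 and 0.31.

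**5. Source of the overstatement.** Interactions kept after the screen average 0.49 for a true 0.40. Power of 66.8% in the fixed model implies 0.40/SE = 1.96 + 0.434, so SE = 0.167. The expected estimate given significance alone is 0.40 + 0.167 × φ(0.434)/0.668 = 0.40 + 0.167 × 0.363/0.668 = 0.49. The P < 0.05 filter explains nearly all of the inflation; the P < 0.20 screen adds little.

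**6. If product terms were screened alone.** A product term carries the arm effect. With no barrier effect and no interaction it still passed P < 0.20 in 47% of trials. In one assumed scenario (40% Black, arm 0.4, race −0.2, interaction 0.25 SD), two simulations with different fitting details kept the interaction in 9% and 10% of trials, against 25% and 34% in the full fixed model.

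**The case against.** The selection sentence speaks of independent variables and never says that product terms are screened univariately. The preceding sentence commits to testing the interactions. A reader might infer that interactions face an invalid univariate test, or are kept without their main effects. The text does not establish this, and the figures in step 6 apply only on that reading. If the interactions were tested whatever the screen showed, the power loss in step 3 would not arise. This objection stands as far as it goes, but the protocol does not state that exemption either, and no reading guarantees that a named term is reported.

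It would also be too strong to say that the rule hides interactions. The last row of the table shows almost no loss when the barrier's overall effect is strong.

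Nor is a twofold exaggeration a general result. It appears for weak effects (0.21 for a true 0.10) and shrinks to about 1.25-fold at 0.20. It comes mainly from low power combined with the significance filter, so a fixed model read only for its significant terms would overstate too. If a main effect drops out, a kept interaction can even be understated (0.32 for a true 0.40 in one run).

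False positives are not a strong argument against the rule. With all interactions null, at least one was kept in 17–18% of trials. Three unadjusted independent tests give 1 − 0.95³ = 14.3%, and the fixed model carries that too.

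An analysis plan that is not shown may say more. The point does not rest on missing detail, however; it rests on a selection rule that the article does fix.

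**Conclusion.** The concern holds in limited form. Named hypotheses are subjected to a selection rule that does not protect them, so a barrier or interaction can vanish from the final model, and what remains has passed a significance filter. The power loss for a real interaction runs from negligible (66% to 65%) to severe (67% to 12%). It is worst when the arm-specific effects cancel or the overall effect is small. These figures rest on the assumed effect sizes, the 35% prevalence, a single barrier per model, and the reading that the barrier is what is screened. Direction is better supported than magnitude.

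Only a secondary aim is affected; the primary comparison of knowledge by arm does not use this rule.

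A separate inconsistency sits alongside. The aim covers one week and three months, whereas the independent effects are to be tested for "health literacy on knowledge at 1 week post-baseline" only, and the interaction sentence gives no time point. The Abstract also lists readiness, self-efficacy and decisional balance "with differences assessed by race", and Secondary analyses describes no such analysis. A reader might infer a commitment to race interactions for those outcomes, but the phrase names no test.

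**What to change.** Replace the selection rule for this aim with one pre-specified linear GEE model containing arm, race, prior actions, health literacy and the three arm-by-barrier interactions, with none of these terms screened. Report every estimate with its confidence interval whatever its p-value, together with the arm effect within Black and within non-Black participants. Confine any selection to additional covariates.

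Fit the model at 1 week and at 3 months, so that Secondary analyses matches Study aims. If race interactions are added for readiness, self-efficacy and decisional balance, label them exploratory and state that multiplicity is not controlled.

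The cost is a change of wording and a few more model runs, with no new data. The interaction estimates will be imprecise: under the step 5 assumptions the 95% interval is about ±1.96 × 0.167 = ±0.33 SD. Reporting it shows readers how much the trial can and cannot say about differences by race.
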